**Fig. 2 Fig2:**
[figure not shown]
Graphical abstract. Figure illustrating the primary and secondary outcomes. The proposed study seeks to evaluate whether early PTA (‘immediate treatment‘ within 48 h) confers benefits over the ‘standard of care‘ elective approach (‘elective PTA‘) in terms of wound healing, and major adverse limb events (MALE) and major adverse cardiac events (MACE), time to complete wound healing, major amputation rate and the need for new revascularization over a follow-up period of one year. Additionally, the study will assess changes in beta-diversity of the wound microbiome and local oxygen saturation and its effects on wound healing

### Research facilities

The Department of Endocrinology and Diabetology and Division of Cardiology, Pulmonology and Vascular Medicine have broad experiences with all clinical and laboratory methods planned for this study. The principal investigators (PI) of the PTA-DFS study are working as specialists in internal medicine, endocrinology, diabetology, angiology and cardiology in both the diabetes foot clinic and the diagnostic and interventional angiology. The clinical research unit at the Institutes provides facilities for all measurements related to this study. The laboratory facilities and corresponding protocols are well-established and routinely used. The associated research unit, the German Diabetes Center (DDZ), offers additional advantages as Germany’s leading diabetes research institution and an internationally renowned facility. It allows for further, yet unspecified, analyses at the cellular level or in mouse models for translational research. All analyses were conducted within a single-center framework (University Hospital Düsseldorf), involving various in-house departments and affiliated specialized centers, all adhering to harmonized workflows and standardized operating protocols to ensure methodological consistency and centralized quality control.

### Main exclusion criteria

Acute leg ischemia (sudden onset, sensorimotor deficits, pale extremity, pain, loss of pulse, and shock)Type 1 diabetes or other forms of diabetes than T2DMinors or individuals incapable of giving consentPregnant or breastfeeding womenTreatment with certain drugs (immunosuppressive therapy, immunomodulators, chemotherapy, antibiotic therapy < 2 weeks before intervention for the microbiome measures)Diseases of the pancreasSevere neurological or psychiatric diseaseKnown presence of malignant tumor disease within the past 5 yearsParticipation in other interventional trials and receipt of investigational medication within the last 30 daysBlood or plasma donation within the previous 3 months

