## Background

Diabetic foot syndrome (DFS) refers to a spectrum of foot pathologies in persons with diabetes, including microvascular and macrovascular disorders. Factors such as distal symmetric polyneuropathy (DSPN), peripheral artery disease (PAD), and immune system impairment increase the risk of soft tissue injuries and infections in diabetic foot ulcers (DFU) [1]. Infected DFU are the leading cause of diabetes-related hospital admissions [2]. The lifetime risk of developing a DFU is reported to be 19–34%, with infections occurring in 50–60% of ulcers [3]. Approximately 20% of diabetic foot infections (DFI) result in lower-extremity amputations, accounting for 44% of minor and 18% of major amputations [4]. Osteomyelitis occurs in 44–68% of hospitalised persons with DFI and is the leading cause of amputation [5].

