## Methods/design

### Study design and randomisation protocol

The PTA-DFS Study is a prospective, monocentric, RCT including participants with T2D and ischemic DFU. Ethics approval was obtained from the local ethics committee (Heinrich Heine University, Düsseldorf, Germany) in accordance with the Declaration of Helsinki (#2022–2291). The PTA-DFS study is registered at www.clinicaltrials.gov (NCT06124586; Registration Date: 2023–08-2).

Participants will be randomly assigned in a 1:1 ratio to either the early PTA group (‘immediate PTA‘ within 48 h after leg artery stenosis (LAS) diagnosis or the elective PTA group (standard of care with PTA within 6 weeks) at the academic hospital of the Heinrich Heine University Düsseldorf, Germany, with inclusion of 200 participants within 5 years. All study participants included in the study will provide informed consent. Although the study is unblinded for both participants and physicians due to practical feasibility, blinding will be applied during the data analysis phase, with separate analysis of primary and secondary endpoints by interventionists (physicians or clinicians) and data analysts to minimise bias. After the data is unblinded, all results will be reviewed collectively. This approach aims to ensure more accurate and unbiased analysis of the primary and secondary endpoints.

Randomisation is performed using a computer-generated sequence with block randomisation to ensure unbiased allocation. The block size will be specified in advance, using blocks of 4 or 6, to maintain balance across groups throughout the study. Both groups receive standard care, with the only difference being the timing of the PTA procedure. The study is structured to ensure that, apart from the timing of PTA, all other aspects of care are consistent across both groups. All subsequent laboratory analyses will be performed in a blinded manner, without knowledge of randomisation. Aside from the timing of PTA, baseline and follow-up examinations will be conducted uniformly across both groups. To optimise recruitment efficiency, training sessions will be held with the interventional angiology staff and the diabetic foot care team, ensuring participants and staff are fully informed about study-related procedures and analyses during their state-of-the-art clinical care.

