### Statistical methods and power calculation

The primary endpoint focuses on the difference in changes of wound area (delta wound area at first - last visit) in T2D participants after early PTA compared to individuals with standard PTA. For the primary—change in wound area after early PTA—and secondary endpoint—combined incidence of MALE and MACE—a power calculation was performed. Assuming a medium effect size (Cohen's d = 0.4), corresponding to 0.4 standard deviations of the difference in delta wound area and difference in time-to-event from baseline to last visit between groups, a sample size of n = 100 per group (total n = 200) is required to achieve 80% power at alpha = 0.05.

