### Recommendations for Timing of Endovascular Therapy in Chronic-Ischemic DFU

The selected time frame for early treatment (within 48 h) was conceptually adapted from the ESC guidelines on non–ST-elevation acute coronary syndrome (NSTE-ACS), which recommend an early invasive approach within 24–72 h to prevent ischemic progression and improve outcomes. While the pathophysiology of coronary artery disease and PAD differs, the underlying principle—namely, that timely reperfusion limits tissue damage—can be applied to the context of critical limb ischemia in patients with DFS. This is supported by an observational study, which indicated that a shorter time to revascularisation (within 8 weeks) is correlated with a higher likelihood of healing in ischemic foot ulcers and limb salvage rates [40]. The time frame for follow-up visits with every 4 week examinations over 3 month is based on a post-hoc analysis suggesting that a four-week evaluation period assessing the percent change in DFU area is a robust predictor of healing at 12 weeks [41].

Limited information exists regarding the prospective outcomes of revascularisation in T2D persons with PAD and DFU. One study showed that persons with PAD who underwent revascularisation were nearly 15 times more likely to achieve wound healing compared to those who did not, with ulcer severity influencing the healing outcome [42]. Delays in revascularisation may exacerbate hypoxic conditions, favouring anaerobic bacterial proliferation, inflammation and impairing wound healing. In addition, the 48-h window represents a clinically feasible and operationally meaningful target in modern multidisciplinary diabetic foot care. Thus, this threshold balances pathophysiological urgency with realistic logistics in specialised vascular settings.

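### The antibiotic exclusion is timed from the PTA, the randomised factor, so its two-week window lies almost wholly before randomisation in the early arm but partly or wholly after it in the elective arm

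*Protocol article*

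**What the plan says.** In the protocol article, Main exclusion criteria, the item on disallowed drugs includes antibiotic therapy less than two "weeks before intervention for the microbiome measures". It stands in the same list as immunosuppressive therapy and chemotherapy.

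Table 1 puts the eligibility screen, consent and randomisation at V0. The intervention has its own PTA column.

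Study design and randomisation protocol sets early PTA within 48 h of diagnosing the stenosis. The other arm is "the elective PTA group (standard of care with PTA within 6 weeks". The same section says that PTA timing is the only intended difference in care between the arms.

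Wound swabs and tissue are taken at V0 and at every later visit (Table 1; Biosample collection and storage). Statistical methods and power calculation compares microbiome change between arms with mixed models, and the Background adds that the baseline microbiome will be explored as a predictor of healing.

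**The concern.** An eligibility criterion should be decidable before allocation and should mean the same in both arms. This one looks back from an event whose date is set by the allocation. For many elective patients the window has not yet begun when eligibility is screened. Two consequences follow if the wording is applied as it stands.

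- **Selection after randomisation.** An elective patient given antibiotics while waiting can come to meet an exclusion criterion. An early patient given antibiotics at the same time after randomisation has usually had the PTA already and cannot. Antibiotic use is related to infection and so probably to prognosis. The Background gives infection as common ("with infections occurring in 50–60% of ulcers"), though that is general epidemiology and not a rate for this trial. Any loss of patients or samples would tend to leave a better-prognosis elective group and count against early PTA.
- **Baseline sampling.** The rule exists for the microbiome data, yet in the elective arm it does not protect the V0 swab, which is the reference for change and for prediction.

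**Working it through.** **1. The plan's own sample size.** The planned effect is d = 0.4 ("corresponding to 0.4 standard deviations of the difference in delta wound area"), with two-sided alpha 0.05, power 80% and 100 per group. By the normal approximation, n = 2(1.960 + 0.842)² / 0.4² = 98.1, so 99 per group; the t-test version gives 99.08, so 100. Power at 100 per group is 80.7% (normal) or 80.4% (t). The stated figure is reproduced. It serves below only as the yardstick of 0.4 SD.

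**2. Share of the window after randomisation.** Assume randomisation close to diagnosis, and PTA on day t after it. The share is min(t, 14)/14.

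| PTA on day | Share after randomisation |
|---|---|
| 0 | 0% |
| 2 (latest for early arm) | 2/14 = 14% |
| 7 | 7/14 = 50% |
| 14 | 14/14 = 100% |
| 42 (latest for elective arm) | 100% |

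The article gives no distribution of elective PTA dates. If they were uniform over days 0 to 42, the window would lie wholly after randomisation for 28/42 = 67% of elective patients, and the mean share would be (14 × 0.5 + 28)/42 = 83%.

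**3. The V0 swab.** An early patient who satisfies the rule has had at least 14 − 2 = 12 antibiotic-free days before V0. For an elective patient with PTA on day 28, the window runs from day 14 to day 28. Antibiotics taken the day before V0 do not breach it.

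**4. Possible effect on the primary endpoint.** This step applies only if the rule removes elective patients from the wound-area analysis. Neither the removed share p nor the prognosis of those removed is in the documents, so every input here is an assumption.

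- *Moderate case.* If those removed heal g SD worse than those kept, the elective mean improves by p × g. With g = 0.5, p = 0.10 gives 0.05 SD and p = 0.15 gives 0.075 SD. Divided by 0.4, that is 13% to 19% of the planned effect.
- *Extreme case.* Suppose exactly the worst-ranked share p on a prognostic scale is removed, and that scale correlates ρ with outcome. The shift is ρφ(z)/(1 − p), with z the normal quantile for p. For p = 0.10, φ(z) = 0.1755, giving 0.10 SD (ρ = 0.5) or 0.16 SD (ρ = 0.8). For p = 0.15, φ(z) = 0.2332, giving 0.14 or 0.22 SD. The largest value is 0.22/0.4 = 55% of the planned effect. The implied gap between removed and kept patients, ρφ(z)/(p(1 − p)), is about 0.9 to 1.6 SD, which is very large.
- *Narrow reading.* If the rule covers only the microbiome data, the shift in wound area is zero.

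Power is a lesser matter. Losing 10% or 20% of the elective arm would lower it from 80.7% to 78.6% or 76.0% (normal approximation).

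**The case against.** A reader might infer that the trial removes infected patients from the elective arm after randomisation and so biases its primary endpoint. The document does not support that, for these reasons:

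- Nothing in it says that the criterion is checked again at PTA or that a randomised patient is withdrawn. Table 1 marks the eligibility screen at V0 only.
- The words about the microbiome measures can be read as confining the restriction to that explanatory work, leaving wound area and MALE untouched.
- Other sections point towards keeping such patients. Elective patients with wound-healing complications cross over rather than leave (Study design and randomisation protocol), and antibiotics are to be studied as an interaction factor on the primary and secondary endpoints (Statistical methods and power calculation).
- The effect is not exclusive to one arm, since up to 2 of 14 days can also fall after randomisation in the early arm. Antibiotic use is only a proxy for infection.

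All of this stands, and it limits the conclusion.

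It can also be said that a screener who does not yet know the arm would apply the window to recent antibiotic use in everyone, so that V0 swabs would be protected equally. Table 1 even labels V0 and PTA with the same time point 0. That may be the intention, but it is not what the criterion says, and PTA may follow V0 by up to 6 weeks in one arm. If V0 was meant, the correction simply states it.

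Finally, analysis sets and sensitivity analyses may be in the analysis plan, and operational detail in the full protocol. That is fair as to detail. The point here is the anchor that the article does state.

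**Conclusion.** The anchor is wrong for a trial that randomises the timing of the PTA. Read literally, the criterion depends on antibiotic use after randomisation, and very unequally: at most 14% of the window in the early arm, 100% for any elective PTA from day 14. It also leaves the elective V0 swab unprotected. These conclusions need only the assumption that randomisation is close to diagnosis.

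What is at risk is the between-arm microbiome comparison. Wound area and MALE are at risk only if the criterion is meant as a whole-trial exclusion and is enforced up to the PTA, and the text leaves that ambiguous. The bias in the primary endpoint cannot be derived from the documents. The range from zero to about 0.22 SD is a set of scenarios, not an estimate, and its upper end needs near-perfect selection of the worst healers. The correction is worth making because it is specific and almost free, not because a bias has been shown.

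**What to change.** 1. Time the antibiotic criterion from V0, before randomisation and baseline sampling, in both arms. The share of the window after randomisation then becomes 0 in both.
2. Say whether the criterion governs entry to the trial or only the microbiome data.
3. State that antibiotics started after randomisation exclude nobody from the primary and secondary analyses.
4. Record antibiotics between V0 and PTA as a post-randomisation event, and handle them in a sensitivity analysis of the microbiome outcomes. Medication is already recorded at baseline and at V2 to V6 (Study protocol, data, and biosample handling; Questionnaires), so the added work is to capture the interval from V0 to PTA.

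The cost is a short amendment; the sample size stays at 200. The small downside is that some elective-arm microbiome samples taken around PTA will be antibiotic-exposed, which the sensitivity analysis addresses. No view is taken on the length of the antibiotic-free period or on antibiotic management.

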### Study protocol, data, and biosample handling

Table 1 outlines key analyses and time points throughout the study. Screening and initial informed consent will be conducted by physicians in the angiology and diabetic foot clinic during outpatient visits at enrolment. A physician will verbally explain the study's objectives, methods, potential benefits, and risks before obtaining written informed consent. The complete medical history of the patient is recorded, including current and previous medications. Additionally, information on lifestyle factors (smoking, alcohol consumption, diet, physical activity, mental health, symptom severity, pain, self-management, diabetes distress, erectile dysfunction, and diabetes burden) as well as social status is collected. Participants undergo physical examination and anthropometric measurements, as well as wound swabs and sampling of deep tissue material from the wound bed for microbiome DNA sequencing. Additional proteomic and metabolomic analyses of the wound biofilm are also planned. Results will be disseminated via presentations at national and international scientific conferences and publications in peer-reviewed journals. We will engage with professional societies and patient organisations to facilitate translation into clinical practice. Participants will be offered a plain-language summary of the study results upon request. The protocol, statistical analysis plan, and de-identified analysis code will be deposited in an institutional repository upon publication. De-identified participant-level data will be made available upon reasonable request following appropriate data-sharing agreements and ethics approvals.

### Biosample collection and storage

Ulcer samples will be obtained using the standardised ‘Levine‘ technique for wound swabs and débridement material collection at baseline and follow-up visits [23]. Serial fasting blood samples will be collected for biobank storage, with consent obtained for subsequent genetic analysis. All biosamples will be preserved at −80 °C until analysis. Biosample collection, processing, and storage follow established Standard Operating Procedures (SOPs). Access to biosamples is regulated by a formal request process, reviewed by the PTA-DFS Study PIs, ensuring ethical compliance. A separate ethical approval for the CARDIAMET biobank (#2023–2525) guarantees adherence to national and international standards, ensuring sample integrity and participant confidentiality.

### Data management and security

Patient data will be securely entered into an electronic database using Research Electronic Data Capture (REDCap), fully compliant with the General Data Protection Regulation. Each participant is pseudonymised with a unique screening identifier and assigned a final study identifier at inclusion. These identifiers are used throughout data collection, storage, and reporting to protect confidentiality. Access to study data follows the same formal request process as biosamples, reviewed by the PTA-DFS Study PIs to ensure ethical and data protection compliance.

### Questionnaires

As part of the study protocol, standardised questionnaires are administered at multiple time points to comprehensively assess psychological status, lifestyle factors, comorbidities, and quality of life. At visits V0, V2, V3, V4, V5, and V6, we collect data on depressive symptoms (using PHQ-9, WHO-5, or ADS-L), diabetes distress, concomitant medication, and the presence or development of comorbidities. At visits V0, V4, and V6, additional assessments include physical activity (via the Baecke Index), smoking habits, dietary behavior (using the Food Frequency Questionnaire), mental health status, quality of life (assessed with the SF-36 questionnaire), and neuropathic symptoms (Neuropathy Symptom Score, NSS). These longitudinal assessments allow for a detailed evaluation of psychosocial and behavioral determinants as well as diabetes-related complications throughout the course of the study.

### Laboratory assessments

Venous blood samples in fasting state are processed immediately under standardised conditions, with comprehensive analyses conducted at the Central Laboratory of the University Hospital Düsseldorf as described [24]. Measurements include electrolytes, renal (creatinine, urea, cystatin C), liver function (ALT, AST, GGT, alkaline phosphatase, bilirubin), lipid profiles (cholesterol, triglycerides, HDL, LDL, Lp(a)), and glucose metabolism markers (HbA1c, insulin, glucose, C-peptide) to assess surrogates of whole-body insulin sensitivity, secretion (e. g. Homeostasis Model Assessment 2) and adipose tissue insulin resistance index [25]. Cardiovascular markers of myocardial damage, cardiac stress, and associated anaerobic metabolism (Troponin T hs, CK, CK-MB, NT-proBNP, lactate), markers of inflammations (CRP, procalcitonin, IL-6), diabetes autoantibodies (glutamate decarboxylase-, tyrosine phosphatase-, islet cell-, and zinc transporter-8-antibodies), erythropoiesis (erythropoietin, folic acid, vitamin B12, and reticulocytes) and iron metabolism (ferritin, transferrin, saturation, soluble transferrin receptor) are also measured. Thyroid function (TSH, free T4, free T3), bone health (25-hydoxy-vitamin D), blood coagulation (Quick, qPTT, fibrinogen, free haemoglobin), and haematological status (complete blood count) are evaluated. Anaemia measures include parameters of red blood cells turnover, formation, (dys)function, and haemolysis. Additionally, lactate and anaemia markers, including red blood cell function and iron status, are assessed to evaluate hypoxia and haemolysis.

### Assessment of microvascular complications

DSPN is often prevalent in DFS and assessed using the Neuropathy Disability Score (NDS), based on the modified Toronto Consensus criteria [26]. An NDS score ≥ 3 points is considered pathological [27, 28]. AI-based fundus photography is performed using a non-mydriatic camera (DRS Plus, Centervue®, Padua, Italy) to screen for diabetic retinopathy and macular degeneration [29, 30]. Utilizing confocal imaging technology, the camera provides high-quality retinal images without pupil dilation [31]. Additional complications, such as diabetic kidney disease, are assessed through urinary albumin levels (> 20 mg/l) and estimated glomerular filtration rate based on cystatin C and creatinine levels.

### Vascular and haemodynamic evaluation

At each clinical visit, haemodynamic parameters are measured, including blood pressure (in both arms after 10 min of rest) and heart rate. Comprehensive vascular evaluations include duplex/Doppler ultrasound of leg arteries, ABI assessments [32] and segmental pulse oscillography to measure perfusion pressure independent of media sclerosis often prevalent in diabetes [33]. In this study, haemodynamically relevant LAS refers to ≥ 50% narrowing of relevant arteries, confirmed by duplex ultrasound and/or an ABI < 0.9, and accompanied by clinical indicators of ischemia such as rest pain or ulceration. Peripheral artery anatomy, revascularised vessel patency, stenosis degree via peak flow velocity, and intimal hyperplasia are assessed using duplex ultrasound [34]. Local microcirculation is measured using near-infrared spectroscopy (NIRS) (SnapshotNIR, Kent Imaging, Calgary, Canada), which provides a non-invasive assessment of oxygen saturation in the affected tissues [34]. During the PTA, liquid biopsies are collected before and after significant vascular occlusions visualised by digital subtraction angiography to evaluate lactate levels for hypoxia severity as well as other biochemical and genetic markers. Of note, in cases of severe renal insufficiency, carbon dioxide angiography may be employed for selective angiography.

